## Abstract

**Background:**

Chronic abdominal pain is the hallmark symptom of chronic pancreatitis (CP), with 50% to 80% of patients seeking medical attention for pain control. Although several management options are available, outcomes are often disappointing, and opioids remain a mainstay of therapy. Opioid-induced hyperalgesia is a phenomenon resulting in dose escalation, which may occur partly because of the effects of opioids on voltage-gated sodium channels associated with pain. Preclinical observations demonstrate that the combination of an opioid and the antiseizure drug lacosamide diminishes opioid-induced hyperalgesia and improves pain control.

**Objective:**

In this phase 1 trial, we aim to determine the safety, tolerability, and dose-limiting toxicity of adding lacosamide to opioids for the treatment of painful CP and assess the feasibility of performance of a pilot study of adding lacosamide to opioid therapy in patients with CP. As an exploratory aim, we will assess the efficacy of adding lacosamide to opioid therapy in patients with painful CP.

**Methods:**

Using the Bayesian optimal interval design, we will conduct a dose-escalation trial of adding lacosamide to opioid therapy in patients with painful CP enrolled in cohorts of size 3. The initial dose will be 50 mg taken orally twice a day, followed by incremental increases to a maximum dose of 400 mg/day, with lacosamide administered for 7 days at each dose level. Adverse events will be documented according to Common Terminology Criteria for Adverse Events (version 5.0).

**Results:**

As of December 2023, we have currently enrolled 6 participants. The minimum number of participants to be enrolled is 12 with a maximum of 24. We expect to publish the results by March 2025.

**Conclusions:**

This trial will test the feasibility of the study design and provide reassurance regarding the tolerability and safety of opioids in treating painful CP. It is anticipated that lacosamide will prove to be safe and well tolerated, supporting a subsequent phase 2 trial assessing the efficacy of lacosamide+opioid therapy in patients with painful CP, and that lacosamide combined with opiates will lower the opioid dose necessary for pain relief and improve the safety profile of opioid use in treating painful CP.

**Trial Registration:**

Clinicaltrials.gov NCT05603702; https://clinicaltrials.gov/study/NCT05603702

**International Registered Report Identifier (IRRID):**

PRR1-10.2196/50513

## Introduction

### Background

Chronic pancreatitis (CP) is a syndrome characterized by inflammation and progressive architectural destruction of the pancreas. This may result in pancreatic fibrosis with concomitant loss of exocrine and endocrine function, regardless of etiology. The most common symptom of CP is debilitating abdominal pain, which may be constant or flare intermittently. The health care and socioeconomic consequences of CP may be substantial. Notably, painful disease exacerbations often prompt medical evaluation. Patients with constant pain often require daily analgesics for pain relief; further, they may experience disability, subsequent loss of productivity, and frequent need for hospitalization [1].

The treatment of abdominal pain is idiosyncratic and typically based on the skill set of the provider or the resources available at an individual institution. The management of pain in patients with CP has traditionally been based on the assumption that all symptoms have a structural basis. However, in a recent review, it was noted that central sensitization and psychological and social factors are now recognized to potentially contribute to chronic pain, supporting the expansion of therapeutic approaches to include nonstructural behavioral interventions [2]. Although the authors recommended avoidance of chronic opioid use in this patient population, opioids remain a mainstay of therapy at many centers in the United States. However, opioid use may present serious risks, including overdose and opioid use disorder. From 1999 to 2014, >165,000 people died of overdose related to opioid pain medication in the United States [3]. In addition, opioid monotherapy is often insufficient for the management of chronic pain of any etiology. Notably, the single-agent maximum-tolerated dose (MTD) of these drugs may reduce pain by only 25% to 40%, owing to incomplete efficacy, dose-limiting adverse effects, or both. The side effects of opioids, including marked detrimental effects on respiratory, gastrointestinal, and cardiovascular functions, may limit the use of opioid analgesia. In 2016, the Centers for Disease Control and Prevention published a guideline for prescribing opioids for chronic pain, noting that nonpharmacological and nonopioid pharmacological therapies are preferred for chronic pain [4]. If opioids are used, they should be combined with nonpharmacological therapy and nonopioid pharmacological therapy, if possible. Therefore, to minimize side effects, clinicians should prescribe the lowest effective opioid dose. Successful development of an opioid-minimizing strategy would provide clinicians with a new tool to lower the prescribed opioid doses*.* Studies addressing the efficacy of alternative methods for pain management are necessary. We propose an innovative study and intervention that focuses on the safety and tolerability of a novel combination of narcotic and nonnarcotic approach to pain experienced by patients with CP.

Adjuvant drugs, including antidepressants and anticonvulsants, are often used in combination with opiates for the treatment of pain with modest outcomes. One rather pronounced adverse off-target effect of opioids is an increasing sensitivity to noxious stimuli, even evolving a painful response to previously nonnoxious stimuli (allodynia). This condition is clinically known as opioid-induced hyperalgesia (OIH) [5,6]. The underlying pathophysiology of OIH is complex and may be mediated by central [7-9] or peripheral [10] pathways. An intervention targeted against 1 or more of these mechanisms may potentially limit OIH and lead to improved pain control in patients requiring opioids. On the basis of preclinical published data [11], preliminary studies presented subsequently, and clinical observations [12], we hypothesize that therapeutic targeting of the sodium channel NaV1.7 will improve opioid efficacy for controlling pain in patients with CP. Voltage-gated sodium channels (NaVs) play a key role in the initiation and propagation of action potentials in electrically excitable nociceptive neurons. Specific NaVs in these neurons can be activated by nonclassical opioid receptors [11,13]. This activation and augmentation of NaV-dependent pain sensing appears to counter a few classical opioid effects [14-16]. Therefore, neuronal activation of NaV1.7 could be one of the mechanisms that limit opioid effectiveness [11,13,15,16]. The activation of these channels can be blocked with an existing class of Food and Drug Administration (FDA)–approved antiepileptic seizure drugs that modulate NaVs [11,17-20]. The recent identification of neurobiological mechanisms associated with NaV1.7 and opioid efficacy provide the innovative rationale for this combinatorial opioid adjuvant therapy. The basic drug mechanism is that nonclassical opioid receptors function to increase the NaV1.7 current in nociceptive sensory neurons, leading to drug-induced pain, or OIH. The combination of an opioid and specific antiseizure drugs such as carbamazepine, oxcarbazepine, or lacosamide effectively diminishes the opioid-induced NaV1.7 current [11,13,15]. These preclinical observations in several neuropathic pain-induced injury models lay the foundation for changing the management of chronic pain from empirical symptom control to personalized targeting of specific mechanisms responsible for pain.

Lacosamide is a first-in-class FDA-approved modified amino acid antiepileptic drug that targets NaV1.7. It was approved by the FDA after phase 3 trials as adjunctive and monotherapy in adults with refractory partial epileptic seizures [21]. The mechanism of action of lacosamide is thought to be that it enhances the slow inactivation of NaV1.7 without affecting its fast inactivation [17-20]. Lower concentrations of this drug may also bind to fast-inactivated states in a manner similar to other antiseizure agents but with slower kinetics of binding and unbinding [20]. Therefore, this means that lacosamide only affects neurons that are depolarized or active for long periods, which is typical of neurons not only at the focus of epilepsy but also central to active pain states. We chose lacosamide as our study drug over other sodium channel inhibitors because it has a favorable side effect profile. Carbamazepine use as an adjunct to opioids is limited by its adverse effects; therefore, the reduced side effect profile of lacosamide may make it a better choice for chronic pain management [22]. In addition, carbamazepine is a well-known inducer of hepatic drug metabolism and therefore may result in a variety of drug interactions that might compromise the efficacy and safety of ongoing therapies. Lacosamide, on the other hand, has minimal interaction with hepatic cytochrome P450 drug-metabolizing enzymes [23]. Lacosamide is a *CYP2C19 substrate* [24]. The drug has a negligible first-pass effect, with a bioavailability of approximately 100%. The maximum lacosamide plasma concentrations occur approximately 1 to 4 hours after oral administration, and the pharmacokinetics of lacosamide are dose proportional. Food intake does not affect its absorption. Notably, *CYP2D6* is responsible for the metabolism of most of the commonly prescribed opiate medications, including codeine, tramadol, hydrocodone, and oxycodone [25]. Furthermore, the *CYP3A4* system regulates the excretion of fentanyl, methadone, and buprenorphine. However, patients receiving methadone will be excluded from participation in Safety, Tolerability, and Dose-Limiting Toxicity of Lacosamide in Patients With Painful Chronic Pancreatitis (STTEPP), as this is a μ-opioid agonist and acts as an antagonist of the N-methyl-D-aspartate (NMDA) receptor [26].

Several studies have evaluated lacosamide as a monotherapy for clinical pain conditions such as fibromyalgia and painful diabetic peripheral neuropathy. Although all studies claimed that lacosamide reduced neuropathic pain and was well tolerated, the outcomes were generally inconclusive and provided only marginal benefits [27-31]. Notably, however, all these studies excluded patients who required opioids for pain control. One clinical case report suggested that chemotherapy-induced painful peripheral neuropathy uncontrolled by opioids alone is accompanied by a dramatic reduction in pain when lacosamide was added to opioid therapy [12]. This provides clinical evidence supporting our rationale for the use of lacosamide in combination with opioids to treat neuron-based symptoms. Therefore, we propose to evaluate lacosamide in conjunction with opioids, which is where evidence consistently shows a benefit. Evidence regarding the effect of lacosamide on NMDA receptor has been shown by its ability to prevent seizures and death in NMDA-induced convulsion test paradigms in mice [32].

### Objectives

In this protocol, we will evaluate the safety, tolerability, and dose-limiting toxicity (DLT) of the combination of lacosamide and opioid therapy in patients with CP, as well as the feasibility of the performance of this phase 1 pilot study. The MTD will be determined. Lacosamide, an anticonvulsant that is safe and well tolerated in patients with epileptic seizures, may potentially lower the opioid dose necessary for adequate pain relief in patients with CP. The positive outcomes of this pilot study will then support proceeding with a phase 2 efficacy trial assessing the ability of opioid adjuvants to alleviate abdominal pain in this difficult patient population. In addition, we believe that this combination therapy will serve to significantly enhance the safety profile of opioid use in these patients.

## Methods

### Study Organization

The Consortium for the Study of Chronic Pancreatitis, Diabetes, and Pancreatic Cancer (CPDPC) has been tasked by the National Institutes of Health (NIH) with the comprehensive clinical, epidemiological, and biological characterization of patients with CP to develop treatments and gain insight into the pathophysiology of CP and its sequelae, including chronic pain, pancreatic exocrine and endocrine insufficiency, and diabetes pancreatic cancer association [33]. All participating clinical centers in the STTEPP trial are CPDPC members and are contributing to a longitudinal cohort study called *Prospective Evaluation of Chronic Pancreatitis for Epidemiologic and Translational Studies* (PROCEED) [34], the first prospective cohort study of pancreatitis in the United States. STTEPP was funded by the National Institute of Diabetes and Digestive and Kidney Diseases (NIDDK; R01DK132709) in April 2022 as a multi-institutional prospective ancillary study within the CPDPC. MD Anderson Cancer Center, University of Texas, will serve as the data coordinating center for STTEPP, and the Institutional Review Board (IRB) at MD Anderson will serve as the single-center IRB for this study. The goal of this clinical research study is to determine whether adding the antiseizure medication lacosamide to opioid pain medications will help in managing chronic, ongoing abdominal pain symptoms caused by CP. The safety of this drug combination will also be studied. This is an investigational study.

### Lacosamide

Lacosamide is a Schedule V controlled substance approved by the FDA for the management of seizure disorders. A controlled substance is a drug or other substance that is tightly controlled by the government, because it may be abused or cause addiction. All controlled substances in the United States are classified into 5 schedules. Schedule V drugs, including lacosamide, have the lowest potential for misuse and addiction compared with those in other schedules. Although it has been used off-label to treat pain resulting from nervous system damage, this medication is not FDA approved for the management of abdominal pain. Currently, it is being used to treat abdominal pain for research only. There may or may not be benefits for participants in this study. The participant will be closely followed by a study coordinator and site investigator during participation. Although the actual drug therapy will only last for 7 days, the participant may experience improved control of their abdominal pain symptoms during the study. Future patients may also benefit from what is learned in this study.

### Ethical Considerations

This study protocol was approved by the University of Texas MD Anderson Cancer Center Institutional Review Board (IRB ID 2021-1197). Informed consent was obtained from all participants or their legal guardians. All methods were performed in accordance with relevant guidelines and regulations.

Participation is completely voluntary. Before choosing to participate in this study, participants should discuss any concerns they may have with the study team, including side effects, potential expenses, and time commitment. The participant can read the full list of potential side effects in the *Possible Risks* section of the consent form.

The participant may choose not to take part in this study, and they do not have to participate. They may withdraw from the study at any time. The participant has the right to choose whether to participate in this research study. They may decide to stop participating in the study once they have started. Leaving the study early will not result in any loss of benefits that they already have. Instead of participating in this study, they may choose to continue with their current medications and plan of care.

### Study Details

#### Who Is Eligible to Take Part in the Study?

Patients with ongoing chronic abdominal pain related to CP, even with opioid pain medication treatment, were asked to participate in the study.

#### How Many Participants Are Expected to Take Part in the Study?

Approximately 24 participants will participate in this multicenter study from approximately 5 institutions. Up to 10 participants will be enrolled at Indiana University.

#### How Long Will the Participation Be? How Long Will It Take to Complete the Study?

If the patient decides to take part in this study, they will complete a screening visit in person to determine if they qualify for enrollment. This visit will take approximately 30 to 60 minutes. After the screening visit, participation will involve an in-person visit that will last 60 minutes. The participant will be asked to take the study medication (provided at no cost) for the 7 days of participating in the study. The participant will also keep a medication diary to confirm when and how they take the study medications and their pain medications. The final study visit will be an in-person follow-up visit on day 8, lasting approximately 60 minutes. The study team will collect medical history and clinical information, draw blood samples, and ask the patient to complete the visit questionnaires as well as medication diaries of all pain medications they take, including the study medication. The research data will be maintained indefinitely.

### Screening Visit

The screening visit will be completed in person and is expected to last 30 to 60 minutes. The protocol for the screening visit has been described in Textbox 1.

Protocol for screening visit.The participant will be asked about the medicines they have used or are now taking, including all prescriptions and nonprescription medications.They will also be asked to provide demographic information (eg, age and ethnicity).They will have blood (approximately 7 teaspoons) collected for routine safety tests. These blood tests are important to determine whether they are eligible to participate in the study and to monitor for possible side effects of the study drug. They should fast (ie, eat nothing and drink only water) for at least 8 hours before this blood investigation.If the patient can become pregnant, they will undergo a urine pregnancy test. To participate in this study, they must not be pregnant.The patient will have an electrocardiogram test performed to measure the electrical function of their heart.They will be asked to complete 4 questionnaires related to pain and how it affects their daily life.They will be given a medication diary to track the medications they take for pain.The study team will review their medical records to confirm eligibility to continue in the study.

### Enrollment Visit

The enrollment visit will be completed in person on day 0 and is expected to last for 60 minutes. The protocol for enrollment visit day and the treatment days 1 to 7 is described in Textbox 2.

Protocol for enrollment visit and treatment days.
**Enrollment visit day 0**
The patient will be asked if they have any health problems other than chronic pancreatitis and what medical or surgical procedures they have undergone in the past.They will be asked to complete 4 questionnaires related to their pain and how it affects their daily life.They will be asked about any health problems they may be experiencing.They will be asked what medications they are taking, including all prescription and nonprescription medications.Patients’ vital signs (eg, heart rate, blood pressure, and temperature), height, and weight will be recorded.They will have a physical examination.If they can become pregnant, they will have a urine pregnancy test.Patients will be given a 7-day supply of the study drug and medication diaries to document all medications taken for pain.
**Treatment days 1 to 7**
The lacosamide tablets can be stored at room temperature. Patients will take lacosamide by mouth, 2 times a day, approximately 12 hours apart. They will be asked to try and take the tablets at the same time on each of the 7 days of the study. The tablets may be consumed with or without food. Patients will be asked to swallow the tablets whole with a glass of water or any other liquid of their choice and not chew them.Patients will be asked to complete daily medication diaries for all medications taken for pain, including the study drug.

### Follow-Up Visit

The first follow-up visit will be completed in person on day 8 and is expected to last for 60 minutes. Subsequently, a follow-up visit will be conducted via telephone on day 21. The protocol for these follow-up visits in described in Textbox 3.

Protocol for follow-up visits.
**Follow-up visit on day 8**
Patients will be asked to complete 4 questionnaires related to pain and how it affects their daily life.They will be asked about any health problems they may be experiencing.They will be asked what medications they have taken, including all prescriptions and nonprescription medications from the enrollment visit day 0.Their vital signs will be recorded.They will have a physical examination.Blood (approximately 7 teaspoons) will be collected for routine safety investigations. They will need to fast before the blood is collected.They will have an electrocardiogram test performed to measure the electrical function of their heart.They will return any leftover study drug doses to this visit, in the original bottles.
**Follow-up on day 21: phone visit**
Patients will be asked about any health problems they may be experiencing.They will be asked what medications they have taken, including all prescriptions and nonprescription medications, from the follow-up visit on day 8.

### Patient Eligibility

Relevant to STTEPP, PROCEED study participants are divided into subcohorts to distinguish the natural history of different disease presentations at the time of admission into the cohort [34]. In STTEPP, we will leverage the resources of the CPDPC by approaching participants already enrolled in PROCEED. This approach will facilitate timely accrual, as these participants have demonstrated an interest in research and willingness to participate in CPDPC studies. Although all participants must meet the criteria for diagnosis of suspected or definite CP as per PROCEED definitions [34], study enrollment will not be limited to participants participating in PROCEED. The STTEPP inclusion and exclusion criteria are listed in Textboxes 4 and 5, respectively.

Inclusion criteria.Written informed consent and Health Insurance Portability and Accountability Act (HIPAA) authorization for release of personal health informationAge ≥18 years at the time of informed consentSuspected (YELLOW 2 or 3) or definite (RED) diagnosis of chronic pancreatitis, as per the Consortium for the Study of Chronic Pancreatitis, Diabetes, and Pancreatic Cancer’s *Prospective Evaluation of Chronic Pancreatitis for Epidemiologic and Translational Studies* (PROCEED) study definition with ongoing symptoms of abdominal painPatients must be maintained on an opioid (except methadone or suboxone) for 4 weeks before enrollment for the treatment of abdominal pain related to pancreatitis, with a daily morphine equivalent dose of 20 mg to 120 mg.Ongoing symptoms of abdominal pain even with opioid use (Visual Analog Score and Brief Pain Inventory average score ≥4, at enrollment)Eastern Cooperative Oncology Group performance status of 0 to 2 (Oken et al [35])Ability to swallow and tolerate oral tabletsFemales of childbearing potential must have a negative pregnancy testThe following laboratory parameters must be met: white blood cell count ≥3.0 K/mm^3^, absolute neutrophil count ≥1.5 K/mm^3^, hemoglobin ≥9 g/100 ml, platelets ≥75 K/mm^3^, creatinine ≤1.5 mg/100 mL, bilirubin ≤1.5 x upper limit of normal (ULN), aspartate transaminase ≤3 ULN, alanine transaminase ≤3 ULN; normal PR interval on baseline 12-lead electrocardiogram.

Exclusion criteria.Participants with indeterminate chronic pancreatitis (YELLOW 1) as per *Prospective Evaluation of Chronic Pancreatitis for Epidemiologic and Translational Studies* (PROCEED) criteriaTreatment with any investigational agent within 30 days before registration or concurrent participation in a clinical trial which involves another investigational agentRapidly escalating pain that requires parenteral (eg, intravenous or intramuscular) opioid therapy within 30 days of enrollmentKnown hypersensitivity or allergic reaction to lacosamide, carbamazepine, or oxcarbazepinePregnant or breastfeedingDiagnosis of epilepsy or a patient who is currently taking antiepileptic drugsAbdominal surgery or pain intervention (eg, endoscopic retrograde cholangiopancreatography with sphincterotomy or stent or stone removal and celiac plexus block) within 90 days of enrollment.Hospitalization for pancreatitis exacerbation or pain management within 90 days of enrollmentPatient who currently takes Suboxone or methadone.Other factors which might explain the patient’s ongoing symptoms, at the discretion of the enrolling physician.History of autoimmune or traumatic pancreatitis or sentinel attack of acute necrotizing pancreatitis which results in suspected disconnected duct syndrome.Primary pancreatic tumors, pancreatic ductal adenocarcinoma, suspected cystic neoplasm (>1 cm in size or main duct involvement), neuroendocrine tumors, and other uncommon tumorsPancreatic metastasis from other malignanciesHistory of solid organ transplant and HIV or AIDSKnown isolated pancreatic exocrine insufficiency (eg, without any eligible inclusion criteria)No medical or psychiatric illnesses or ongoing substance abuse that, in the investigator’s opinion, would compromise participant’s ability to tolerate study interventions or participate in follow-up.

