### Objectives and End Point

Our primary objectives are to (1) evaluate the safety, tolerability, and DLT of lacosamide in combination with opioids in patients with CP and (2) assess the feasibility of the performance of a pilot study of adding lacosamide to opioid therapy in patients with CP. As a secondary, exploratory objective, we will assess the efficacy of adding lacosamide to opioid therapy for the treatment of abdominal pain because of CP. The safety end point includes toxicity and DLT of the combination of lacosamide and opioids, defined as grade 3 or 4 toxicities, according to the National Cancer Institute Common Terminology Criteria for Adverse Events v5.0. Tolerability will be assessed by compliance with the intervention. The participants will be evaluated for completing the 7-day trial. The percentage of participants taking 100%, 75%, 50%, and <50% of the study tablets will be recorded. The feasibility end point will include the recruitment rate (ie, the proportion of eligible patients who agree to participate) and the dropout rate, including a qualitative assessment of barriers to retention. The efficacy end point will be assessed using the Visual Analog Score; Brief Pain Inventory, short form, average score; and the Comprehensive Pain Assessment Tool, short form [36] total score. A 50% decrease in pain scores from baseline at study completion will be deemed clinically meaningful. In addition, opioid use will be evaluated, with a decrease of 25% in pain scores from baseline at study completion, identified as clinically significant.

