### Study Visits

A screening visit for eligibility in person or via telephone will occur at 7 to 30 days prior to enrollment. There will be 2 in-person study visits. During study visit 1 on day 0, baseline study assessments and questionnaires will be completed in person. Drug treatment days will then occur from days 1 to 7. During study visit 2 on day 8 (with a 3-day window), following completion of the 7-day drug treatment period, participants will have a face-to-face clinic visit, where similar assessments and questionnaires will be completed, as per the study calendar (Table 2). Participants will return all unused drugs during this visit for disposal and to monitor compliance.

**Table 2 table2:** Study calendar.

		Screening visit, from 7 to 30 days	Enrollment visit, day 0	Treatment days 1-7	Follow-up visit, day 8 (+3-day window)

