**Questionnaires**					
	Physician questionnaire		✓		
	Study coordinator questionnaire		✓		✓
	Patient questionnaire (VAS^f^, BPI^g^, PROMIS^h^, and COMPAT^i^)	✓	✓		✓
	Medication diary	✓	✓		✓

^a^Medical history and establishment of suspected or definite chronic pancreatitis diagnosis may occur at any time before trial entry.

^b^ECOG: Eastern Cooperative Oncology Group.

^c^EKG: electrocardiogram.

^d^Will include at a minimum: electrolytes, glucose, blood urea nitrogen, creatinine and creatinine clearance, calcium, and hepatic function panel.

^e^Will include detailed use of rescue pain medications and opioids use.

^f^VAS: Visual Analog Score.

^g^BPI: Brief Pain Inventory.

^h^PROMIS: Patient-Reported Outcomes Measurement Information System.

^i^COMPAT: Comprehensive Pain Assessment Tool for Chronic Pancreatitis.

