### Statistical Plan and Analysis

A sample size of 24 was determined and calibrated based on the simulation such that the phase 1 trial has reasonable accuracy (>60% probability) to correctly identify the MTD across a set of practically plausible scenarios. We will use descriptive statistics to summarize the demographic and clinical characteristics of the patients. Safety data will be tabulated by the grade and type of toxicity using descriptive statistics, including mean, SD, and 95% CI. The reduction in pain scores will be summarized by the dose using the mean and 95% CI. As an exploratory analysis, *t* test (2-sided) or Wilcoxon rank-sum test will be used to compare the reduction in pain scores between the doses. The recruitment and dropout rates will be calculated for all patients and by dose and used to determine the feasibility of the treatment. Although the data generated will not have a comparator group (ie, no placebo), these will be helpful in understanding the variability of responses in patients with suspected or definite CP, which in turn will be useful for sample size calculation for a follow-up trial.

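### The day-0 pain score is both the entry test and the baseline, so the uncontrolled pain reduction within each dose is biased modestly toward benefit

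*Protocol article*

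**What the plan says.** Patient Eligibility (Textbox 4) requires a "Visual Analog Score and Brief Pain Inventory average score ≥4, at enrollment". The Enrollment Visit section fixes the timing: "The enrollment visit will be completed in person on day 0". Study Visits adds: "During study visit 1 on day 0, baseline study assessments and questionnaires will be completed in person".

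VAS and BPI average are also efficacy measures under Objectives and End Point, together with the COMPAT total score. The responder rule there is: "A 50% decrease in pain scores from baseline at study completion will be deemed clinically meaningful". A second threshold is stated "with a decrease of 25% in pain scores from baseline at study completion, identified as clinically significant", in a sentence that begins with opioid use. Under Statistical Plan and Analysis, "The reduction in pain scores will be summarized by the dose using the mean and 95% CI". That section acknowledges that there is no comparator and expects the data to help size a follow-up trial.

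An earlier pain score exists. At the screening visit, 7 to 30 days before enrollment, "They will be asked to complete 4 questionnaires related to pain and how it affects their daily life". Table 2 ticks the patient questionnaire, including VAS and BPI, at screening, day 0 and the day-8 follow-up. The article gives the screening scores no role in the efficacy summary.

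**The concern.** A person whose pain varies from week to week is more likely to pass a cut-off on a bad day. If the score from that day is also the starting point, part of the later fall only undoes the selection. In a randomized trial both arms share this fall and it cancels. Here nothing cancels it.

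What is at stake is the within-dose mean reduction and the share reaching a 50% decrease. These are the exploratory efficacy output, and the article expects the results to support a phase 2 efficacy trial. A reduction that is partly selection could lead to too hopeful an assumed effect. The article mentions the missing comparator but not this selection effect, part of which can be addressed with data already collected.

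**Working it through.** The article states no figure for pain reduction, so there is none to reproduce. Its sample size of 24 was calibrated on finding the maximum tolerated dose and is not in question here.

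**Inputs from the article.** Cut-off 4, tested on day 0. Baseline on day 0, follow-up on day 8, screening 7 to 30 days before day 0. No placebo group. Four dose levels (100 to 400 mg/day in steps of 100), cohorts of 3, at most 24 participants, stop when one dose has 15.

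**Assumptions, not in the article.** A 0-10 scale; before selection, mean 5-6 and SD 2-2.5; correlation r between visits 0.5-0.8; no drug effect; one score tested.

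**Step 1, size of the bias.** With c = (4 − mean)/SD, the expected fall from day 0 is (1 − r) × SD × φ(c)/(1 − Φ(c)).

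| Mean, SD, r | c | φ(c)/(1 − Φ(c)) | Expected fall |
|---|---|---|---|
| 5, 2.5, 0.5 | −0.40 | 0.368/0.655 = 0.562 | 0.5 × 2.5 × 0.562 = 0.70 |
| 5.5, 2.25, 0.65 | −0.67 | 0.319/0.748 = 0.427 | 0.35 × 2.25 × 0.427 = 0.34 |
| 6, 2, 0.8 | −1.00 | 0.242/0.841 = 0.288 | 0.2 × 2 × 0.288 = 0.12 |

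Simulation on a clipped 0-10 scale gives the same range. With whole-number scores the values are somewhat smaller: 0.05 to 0.41 for mean 5-6, SD 2, r 0.5-0.9.

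**Step 2, confidence intervals.** In the worst case the SD of change is 2.24. The planned intervals are by dose. Simulated t intervals cover 94% at n = 3, 91% at n = 6 and 80% at n = 15 in the worst case, and 95%, 93% and 90% in the middle case. Pooling all 24 gives a standard error of 2.24/√24 = 0.457 and a bias of 0.70/0.457 = 1.53 standard errors. Coverage is then about Φ(1.96 − 1.53) − Φ(−1.96 − 1.53) = 67%, but the article plans no pooled interval.

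**Step 3, responders.** With no drug effect, 0.7% to 12.2% reach a 50% decrease from day 0. Much of this is ordinary noise. With mean 5, SD 2, r 0.7 and whole-number scores, 5.6% reach it when entry and baseline are both day 0, against 3.8% when entry rests on the screening score. Selection accounts for 5.6 − 3.8 = 1.8 percentage points. For a 25% decrease in pain the figures are 23.0% and 18.9%, a difference of 4.1.

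**Step 4, averaging the screening and day-0 scores.** The bias from the averaged baseline is the mean of the biases from its two parts.

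- *Equal correlation between all visits.* Bias from screening is 0.00, so the average gives 0.06 to 0.35 instead of 0.12 to 0.70. The SD of change falls by about 9-12% (worst case 2.24 to 2.04).
- *Correlation decaying with time, middle case.* Bias from screening alone is −0.17 with a 14-day gap and −0.43 with a 30-day gap. The average gives (0.34 − 0.17)/2 = 0.09 and (0.34 − 0.43)/2 = −0.05. The SD of change rises from 1.76 to 1.93-1.98, and the share of false 50% responders does not fall (4.7% from day 0, 4.9% averaged).
- *Same cut-off also applied at screening, middle case.* Bias is 0.25 from day 0, 0.24 from screening and 0.24 from the average. Nothing is gained.

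With selection on day 0 only, and correlation equal, decaying or mixed, the averaged baseline brings the absolute bias from 0.12-0.70 down to 0.00-0.39 points.

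**The case against.** The last pre-dose value is a conventional baseline. Efficacy is exploratory, and the article says openly that there is no comparator. No single sentence names the day-0 score as the efficacy baseline; that follows from Study Visits. Deriving a baseline from several pre-treatment scores is ordinary analysis-plan content, and neither that plan nor the full protocol is shown. Screening may be by telephone, so its score may differ in mode from the in-person scores. Study Measurements says that forms completed before enrollment confirm eligibility, so sites may in practice also screen out low scores earlier. Placebo response and natural course stay in the reduction under any baseline.

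All of this stands as a limit on the weight of the point, and it keeps the severity low. It does not remove the point: the article itself fixes the pain test at enrollment, calls that day's questionnaires baseline, and sets its thresholds from baseline.

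Four stronger readings are tempting, and the article does not support them:

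- **The intervals are badly wrong.** The 67% figure needs a pooled interval at n = 24 and the worst assumed inputs, while the plan summarizes by dose.
- **A screening-only baseline removes the bias.** That needs equal correlation and no selection at screening. With decay it overshoots, to as much as −0.57 points across the settings tried.
- **The SD of change is needlessly large, so the next trial will be mis-sized.** Averaging can raise or lower the SD.
- **The dose comparison is biased.** Every cohort faces the same entry test, so it is not, in expectation.

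**Conclusion.** The point holds in a limited form. Within-dose mean reductions and responder shares are biased toward benefit, by about 0.1 to 0.7 points under the assumed mean, SD and correlation, none of which the article gives. The bias is smaller if typical pain lies well above 4 or scores are very stable. The calculation tests one score, whereas the criterion names both VAS and BPI; COMPAT is not part of the entry test and would be affected only through its correlation with those scores. The loss of coverage is small in small dose groups and becomes noticeable only in the worst case at a dose that reaches its cap of 15. Between-dose comparisons, the maximum tolerated dose, safety and feasibility are unaffected. This is a worthwhile improvement, not a flaw that threatens the trial.

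**What to change.** Leave the entry test as it is. In the analysis:

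- Report the mean reduction with its 95% CI, and the 50% rule, by dose with baseline defined as the mean of the screening and day-0 scores, alongside the change from day 0.
- Show the untreated change from screening to day 0. Under equal correlation, the worst case predicts an untreated rise of 0.70 − 0.00 = 0.70 points, matching the later fall. A change near zero does not prove that the bias is absent, because applying the cut-off at both visits would also produce it (0.25 − 0.24 = 0.01 in the middle case).
- State whether the cut-off is also applied at screening, and record whether the screening score was taken by telephone. If the cut-off is applied at both visits, say that the averaged baseline does not reduce the bias.
- Add one sentence saying that placebo response and natural course remain in every version.

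The cost is analysis wording and one extra column per table; no visit, questionnaire or participant is added. The reported reduction becomes slightly smaller. The SD of change may be somewhat larger if correlation decays over the 7-30 day gap, and the share of false 50% responders may then not fall.
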